#### Primary outcomes

Parent’s psychopathology at 18 months after randomization will be measured by the German version of the Structured Clinical Interview for DSM-IV Axis I Disorders (SCID-I) [21]. The SCID-I is a standardized semi-structured interview for diagnosis of major mental disorders according to DSM-IV Axis I. A trained external rater (blind to the family’s group assignment) will perform the SCID-I by interviewing the parents on their psychopathology.

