**Fig. 1 Fig1:**
[figure not shown]
Study design

If the family is assigned to the intervention group, the therapist who carries out the CARE-FAM and/or WEP-CARE program will be informed, and the start of the intervention will be initiated. If the family is assigned to the control group, no further treatment will be provided within the CARE-FAM study.

At 6 (T2), 12 (T3) and 18 (T4) months after randomization, the families will be contacted again by the research staff. The majority of questionnaires and diagnostic interviews for all three follow-up assessments are the same as at the baseline assessment. Furthermore, after 18 (T4) months external medical data (e.g. treatment data) and cost data from the participating health insurance companies is requested.

For quality assurance, site visits will be conducted in all study centers by principal investigators of CTC North to monitor study progress and compliance with the predetermined regulations of the study.

Study data of each study center will be collected and managed by the study center in Hamburg. The study center Hamburg will receive the original and scanned files from all other study centers. The electronic file will remain in the respective study center. Data will be collected on paper and entered into the electronic case report form (eCRF) provided by secuTrial®, which is designed by CTC North. This data entry system will be password-protected and accessible only to the database managers and study team. To ensure complete and accurate data, visual inspection of the data collected on paper will be carried out before data entry. Trained personnel will carry out the data collection via double entry. Afterwards a third person will review the double data entry. In cooperation with CTC North automated rules for detecting inconsistencies in the data will be integrated and validated by a defined Data Validation Plan.

All study-related information will be stored securely at the respective study center. All records that contain names or other personal identifiers, such as informed consent forms, will be stored separately from study records identified by code numbers. The coordinating study center will oversee the intra-study data sharing process.

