The primary outcome, parent’s psychopathology measured by the SCID-I, is evaluated according to the intention-treat (ITT) principle. The ITT population consists of all randomized families for which baseline documentation is available. As the members of a family live under common conditions and interact with each other, cluster effects can be assumed. Thus, the inferential statistics are performed with mixed models. The primary outcome is binary (diagnosis according to SCID-I yes/no). A mixed logistic regression with family and family member as random effects, recruitment center, therapy group (2 factors: 1st factor CARE-FAM yes/no, 2nd factor WEP-CARE yes/no), and time as fixed effects within the ITT population of all initially conspicuous parents is performed. The interactions between time and the therapy groups is determined. If they are not significant, they are eliminated from the model. Missing values are treated by direct imputation to allow an ITT analysis. Under the assumption of two stochastically independent interventions, the contrast of each group factor at T4 is tested at the 5% level (two-sided hypothesis). Thereby, each intervention can prove to be effective on its own. Only these results are interpreted in a confirmatory manner. In an additional analysis, we test the assumption of independence by examining the interaction between both therapy group factors. The primary analysis is repeated in the per protocol population, which consists of all families with at least three sessions in CARE-FAM or WEP-CARE. To assess the effect of the interventions within specific subgroups, the following subgroup analyses are performed regarding study center, disease of children, age of the children, and disease of parents. In a series of sensitivity analyses, missing values are imputed by different approaches as last observation carried forward, multiple imputation, worst- and best-case imputations. Secondary outcomes are investigated exploratively without adjustment for multiplicity in the ITT population. The analysis strategy for the secondary, binary outcomes is the same as in the primary analysis. For secondary, continuous outcomes, linear mixed models with differences to baseline as outcome, family and family member as random effects and the same fixed effects as in the above-mentioned model and respective baseline value as covariate are examined. The safety outcomes are determined using frequency tables and if possible, with mixed logistic regression analogue to the primary analysis. Odds ratios or adjusted means, their 95% confidence interval, and *p* values are reported according to the CONSORT statement. Interim analyses are not planned. Statistical analyses will be carried out with standard statistical software.

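### Dropping non-significant time-by-therapy interactions replaces the confirmatory 18-month contrast with an effect pooled over visits, so a benefit that has faded can be declared present at 18 months

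*Protocol article*

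**What the plan says.** The Primary outcomes section fixes the time point: "psychopathology at 18 months after randomization will be measured" by SCID-I interview. The Sample size section powers the trial on the same time point, with 91.2% against 80% of initially conspicuous parents no longer conspicuous. The follow-up visits are given under Data assessment and data management: "At 6 (T2), 12 (T3) and 18 (T4) months after randomization, the families will be contacted again by the research staff".

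The Data analysis section specifies a mixed logistic regression in the initially conspicuous parents. Family and family member are random effects; centre, the two therapy factors and time are fixed effects. It then states: "The interactions between time and the therapy groups is determined. If they are not significant, they are eliminated from the model". The confirmatory step follows: "the contrast of each group factor at T4 is tested at the 5% level", two-sided, and only these results are to be read as confirmatory.

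No level is given for the elimination step. Nothing in the article says that the T4 contrast is taken from a model that still contains the interaction.

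**The concern.** The two instructions do not fit together. A contrast at T4 differs from a contrast at any other visit only if the model lets the therapy effect vary over time. With the interaction removed, the T4 contrast is the common effect over all visits, so data from 6 and 12 months determine most of it.

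Three consequences follow.

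- A preliminary test in the same data chooses the estimand, and the reported p-value and interval ignore that choice.
- A short-term benefit that has gone by 18 months can still produce a significant result labelled 18 months.
- A benefit that builds up late is diluted.

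Fading is a realistic possibility. CARE-FAM runs over six months and WEP-CARE over 12 to 14 weeks, so T4 comes about a year after treatment ends (18 − 6 = 12 months for CARE-FAM), while T2 falls at or near its end. These contrasts are the trial's only confirmatory results, and the Discussion aims at implementation in regular care throughout Germany.

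**Working it through.** **1. The algebra.** Write the fixed part of the model for one factor (CARE-FAM, C = 0/1) as logit P = centre + γ_t + β·C + δ_t·C, with δ_t = 0 at a reference visit. The T4 contrast is β + δ_T4. If the δ terms are eliminated, the contrast is β at every visit, and the fitted β is a precision-weighted common log-odds ratio over the visits. The same holds for WEP-CARE.

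**2. The protocol's own sample size.** Inputs from the Sample size section: 80% against 91.2%, two-sided 5%, power 80%, 74 parents per combination group (2 × 74 = 148 per factor level), 30% conspicuous, 20% dropout.

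- Unpooled formula: n = (1.960 + 0.842)² × (0.80×0.20 + 0.912×0.088) / 0.112² = 7.849 × 0.2403 / 0.01254 = 150.3, so 151 per level. The pooled formula gives 154.
- Exact binomial power at 148 per level is 80.0%.
- 74 / 0.30 = 246.7, rounded up to 247; 4 × 247 = 988. Then 247 / 0.80 = 308.75, rounded up to 309; 4 × 309 = 1236, or 618 families with two parents each.

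The stated figures reproduce. They rest on the 18-month comparison alone, with no gain from pooling visits.

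**3. Assumed fades on the odds scale.** Protocol effect: (0.912/0.088) / (0.80/0.20) = 10.36 / 4 = 2.59. Halfway (85.6%): (0.856/0.144) / 4 = 5.94 / 4 = 1.49. No effect at T4: odds ratio 1.

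**4. Simulation of the written rule.** There were 148 parents per level and 20,000 trials per scenario. Correlated binary outcomes at T2, T3 and T4 came from a latent normal model with common correlation ρ. In each trial, L is the vector of three log-odds ratios and V its covariance.

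- Test time-by-factor with a 2-df Wald test at 5%.
- If significant, test L_T4 against its standard error.
- If not, test the common effect (1ᵀV⁻¹L)/(1ᵀV⁻¹1), with variance 1/(1ᵀV⁻¹1).
- The comparator always tests L_T4.

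The rates before T4, the values of ρ and the 5% level for elimination are assumptions, because the article gives only the 18-month rates. Comparison rates are 80% at every visit.

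| Treated rates at T2/T3/T4 (%) | Quantity | ρ=0.3 | 0.5 | 0.7 | 0.85 |
|---|---|---|---|---|---|
| 91.2/85.6/80 (gradual fade) | interaction retained | 49.0% | 56.6% | 67.7% | 80.8% |
| | rejects, written rule | 26.0% | 18.4% | 12.3% | 7.6% |
| | rejects, interaction always kept | 4.9% | 4.4% | 4.6% | 4.7% |
| 91.2/91.2/80 (late loss) | interaction retained | 65.9% | 73.2% | 82.9% | 92.2% |
| | rejects, written rule | 27.3% | 19.6% | 11.6% | 6.5% |
| | rejects, interaction always kept | 4.6% | 4.7% | 4.8% | 4.5% |
| 80/80/80 (no effect) | rejects, written rule | 5.8% | 5.3% | 5.2% | 5.0% |
| 80/85.6/91.2 (growing) | power, written rule | 69.6% | 67.7% | 69.5% | 72.5% |
| | power, interaction always kept | 78.6% | 78.1% | 78.6% | 78.4% |
| 91.2/91.2/91.2 (constant) | power, written rule | 97.0% | 95.5% | 92.4% | 88.3% |
| | power, interaction always kept | 78.5% | 78.1% | 78.7% | 78.9% |

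In the gradual fade, trials that dropped the interaction gave a mean pooled odds ratio of 1.37–1.47, against a true value of 1 at T4.

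**5. Sensitivity.** If comparison parents recover over time (60/70/80%) and treated parents recover sooner (75/80/80%), the written rule rejects in 39.7%, 32.8% and 25.4% of trials at ρ = 0.3, 0.5 and 0.7, against about 5% with the interaction kept. A small run with a one-factor random-intercept logistic model (250 trials per scenario) gave about 11–27% under assumed fades.

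**The case against.** Several points can fairly be made for the plan.

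- With no effect at any visit, the rule almost keeps its level (5.0–5.8%). The inflation needs an early benefit, little or no benefit at T4, and an interaction test that misses the fade.
- The interaction test is not weak in these scenarios. It detects the fade in 49–92% of trials, and at very high within-parent correlation little harm remains (6–8%).
- The earlier-visit rates and correlations are not in the article. The main simulation is marginal, handles one factor, and ignores family clustering, centre and missing data, so its percentages are indicative.
- If the effect is constant, pooling raises power from about 79% to 88–97%.

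All of this stands as a limit on the size of the problem. None of it removes the contradiction, because after elimination the T4 contrast is not specific to T4 under any assumption about rates or correlation. The random-intercept run shows that the inflation does not come from the marginal approximation. Nor is this a detail left to the analysis plan: the article states the rule, and a plan that follows it inherits the problem. The gain in power applies to a different quantity from the one the trial declares primary.

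**Conclusion.** The point holds. The article declares an 18-month effect as the confirmatory quantity and then lets a preliminary test replace it with an effect pooled over visits.

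Under the two assumed fades with no true effect at 18 months, the false-positive rate at T4 is about 12–27% for correlations of 0.3–0.7 and 6–8% at 0.85, instead of about 5%. The recovering-comparison scenario gives more. For a growing effect, T4 power drops by about 6 to 10 percentage points.

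These sizes depend on the assumed rates and correlations; the change of estimand does not. Because it affects the only confirmatory tests, it should be corrected before the analysis.

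**What to change.** Delete the elimination rule. Specify time as a categorical factor with T2, T3 and T4 as the outcome visits, keep both time-by-factor interactions in the primary model whatever their p-values, and test the T4 contrast of each factor from that model. Report the effect pooled over visits as a supportive analysis. Naming the outcome visits also settles whether time includes baseline, where every parent in this analysis set is conspicuous by definition.

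The secondary outcomes use the same strategy or the same fixed effects. They are exploratory, so changing them too is for consistency.

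The change is one of wording. Sample size and stated power stay as they are, since both rest on T4 alone. The cost is the unplanned gain under a constant effect: about 79% power instead of 88–97%.

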### Study design

The study is a prospective, 2x2 factorial randomized controlled multicenter superiority trial. With assessments at baseline as well as at 6, 12, and 18 months after randomization, the family-based intervention programs CARE-FAM, WEP-CARE and the combination CARE-FAM + WEP-CARE are evaluated against a control group in terms of their effectiveness and efficacy. All families have the possibility to use routine care services. Therefore, families in the control group receive treatment as usual (TAU), meaning they do not receive any intervention within this study. Outcomes will be assessed from the parents’, patient’s, and siblings’ perspective as well as from the therapist’s perspective. The primary outcome of the study will be assessed by external, blinded raters.

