The program is concluded with about three sessions for the whole family, which are the core of the CARE-FAM intervention. These sessions include all family members and aim to bring together all individual perspective’s findings from the single sessions. At the same time, openness, transparency and communication within the whole family can be encouraged. The family’s present and future handling of the disease and support from inside and outside the family can be reflected on and responded to. Depending on the family’s needs and wishes, individual topics like current conflicts can also be discussed. If any family member or the whole family needs further treatment or support, additional aids will be initiated by the program staff. If participants agree, all intervention sessions will be video-recorded for quality control reasons. All therapists are experienced in the field of adult or child and adolescent psychiatry and received a comprehensive two-day training based on the CARE-FAM manual. Adherence to the intervention manual will be enhanced by continuous supervision. During the corona pandemic, in-person therapy sessions will be replaced by online video sessions whenever possible.

The goals of the CARE-FAM program can be structured into the three subsequent levels: coping, relationships and family dynamics. On the (1) coping level, the main aims are the reinforcement of coping strategies for the handling of the child’s disease and discussions about important events maintaining conflicts inside the family, such as hospitalization, loss of employment or change of residence. On the (2) relationship level, the main aims are to overcome social isolation and strengthen intra-familial relationships. On the level of (3) family dynamics, the main aims are to promote the understanding of the disease and the couple and family dynamics from a psychodynamic, multi-generational perspective.

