#### WEP-care

WEP-CARE is a manualized supportive online intervention addressed to parents of chronically ill children and adolescents [15, 18, 19]. WEP-CARE is based on well proven principles of cognitive-behavioral writing therapy and is conducted entirely via the internet. The aim of the intervention is to support parents with the psychosocial management of their child’s disease. By reducing parents’ psychological complaints such as anxiety symptoms, depressive symptoms or stress symptoms, quality of life as well as the whole family’s ability to cope with the disease will be improved. In the long term, parents should master everyday life with a chronically ill child more easily. As the intervention reduces the psychological burden of the parents, it will also have positive effects on the affected children and their siblings.

With the support of therapists trained in this program, the participants carry out 12 standardized writing tasks of about 45 min at approximately weekly intervals in a time period of 12 to 14 weeks, on a data-secured internet platform. The therapists give individualized feedback within 48 h with further instructions. This feedback is supervised within the framework of continuous supervision to guarantee adherence to the intervention manual. The main focus of the intervention lies on overcoming fear. Within the writing tasks well established behavioral and cognitive techniques are used, as for example exposition, cognitive restructuring or problem-solving training. Furthermore, by establishing positive activities, resource activation and drawing attention on positive occurrences concerning the disease, depressive symptoms are also addressed. The following topics are covered within the 12 writing tasks of the program: current handling of the disease, overcoming fear, problem solving, self-care and stabilization as well as integration of what has been achieved. WEP-CARE was successfully evaluated in a pilot study with parents of children affected by cystic fibrosis [15, 20] and implemented in a generic adaptation for parents of chronically ill children. Results showed large effects of anxiety reduction and medium effects of improved depression and quality of life of affected parents.

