#### Control group

Families who have been randomly assigned to the control condition will receive TAU. They will receive the standard treatment that is normally given in regular care but no additional intervention within this study. All participating families in the control group and intervention groups are not prohibited from seeking additional treatment or additional interventions outside of the study.

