#### Randomization and blinding

Computerized lists for familywise randomization with variable block length stratified by recruitment centers are prepared by the Department of Medical Biometry and Epidemiology of the University Medical Center Hamburg-Eppendorf. According to a 2x2 factorial study design, each family is randomized to one of four combinations of the two interventions (CARE-FAM only, WEP-CARE only, combination, no study intervention). The subsequent central allocation procedure will be managed by the coordinating study center in Hamburg to guarantee allocation concealment. Randomization will take place once the standardized baseline diagnostics are complete. Thus, every randomized family received comprehensive standardized diagnostics of every participating child and parent. This will maintain the families’ interest in the study and enhance retention. Although families will be aware of the group they have been assigned to, the external raters assessing the primary outcome and the health-economics will be blinded regarding the families’ group allocation to avoid detection bias by project members.

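### As written, the per-protocol rule excludes every control family that follows its assignment, so the supportive repeat of the primary analysis has no TAU group

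*Protocol article*

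**What the plan says.** All references are to the protocol article.

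- **Data analysis** states that "The primary analysis is repeated in the per protocol population" and defines that set as the "per protocol population, which consists of all families with at least three sessions in CARE-FAM or WEP-CARE". The analysis repeated is a mixed logistic model with two yes/no factors, CARE-FAM and WEP-CARE, in initially conspicuous parents.
- **Randomization and blinding**: "each family is randomized to one of four combinations of the two interventions (CARE-FAM only, WEP-CARE only, combination, no study intervention").
- **Study design**: "families in the control group receive treatment as usual (TAU), meaning they do not receive any intervention within this study". **Control group** agrees: "They will receive the standard treatment that is normally given in regular care but no additional intervention within this study". The text after Figure 1 (Data assessment and data management) adds: "If the family is assigned to the control group, no further treatment will be provided within the CARE-FAM study".
- **WEP-care** describes the online programme in tasks: "the participants carry out 12 standardized writing tasks". The per-protocol rule counts sessions.
- **Sample size** plans 155 families and 74 initially conspicuous parents in each of the four groups, and assumes that the two interventions work independently.

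**The concern.** A per-protocol set should hold the families in each arm that received what they were assigned. For a control family, that means no study sessions. The stated rule does the reverse: the families that complied with TAU are the ones it removes, and a control family could enter only by receiving study sessions contrary to its assignment.

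An analyst who applies the sentence literally would delete one randomised arm and fit a two-factor model to the other three. The result would be reported beside the ITT result as if it answered the same question, although no untreated group is in it.

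The combination arm has a related problem. With *or*, three sessions of one programme and none of the other are enough to qualify, yet the family is coded yes on both factors. In the set meant to reflect treatment received, that family counts as treated with a programme it did not take up.

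**Working it through.** **1. The plan's own figures.** Inputs from Sample size: 91.2% against 80%, two-sided 5%, power 80%, 74 conspicuous parents per cell (148 per factor level, 296 in total), 30% conspicuous at baseline, 20% dropout.

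- Unpooled normal approximation: n = (1.96 + 0.8416)² × (0.912 × 0.088 + 0.80 × 0.20) / 0.112² = 150.3, so 151 per level and 302 in total. This is 2.0% above the stated 296.
- Families: 296 / 0.30 = 987 (stated 988); 988 / 0.8 = 1235 (stated 1236); 1236 / 2 = 618, rounded to 620 = 4 × 155.

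The figures reproduce closely enough to use 74 parents and 155 families per cell below.

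**2. The rule applied to each arm.**

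| Arm | Study sessions if the assignment is followed | Can it qualify? |
|---|---|---|
| CARE-FAM only | CARE-FAM | yes |
| WEP-CARE only | WEP-CARE | yes, if tasks count as sessions |
| Combination | both | yes, even on one programme alone |
| No study intervention | none | no |

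With full adherence in the three active arms, at most 3 × 155 = 465 of 620 families and 3 × 74 = 222 of 296 conspicuous parents remain. The loss by definition is 155 / 620 = 25% of families.

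**3. What the model then estimates.** Write m11, m10, m01 and m00 for the cell values of combination, CARE-FAM only, WEP-CARE only and TAU. Take n parents per cell and a common variance s².

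- Four cells, additive model: CARE-FAM effect = ½[(m11 − m01) + (m10 − m00)]. Variance = ¼ × 4s²/n = s²/n. The comparison is 148 against 148.
- Three cells, additive model: there are three parameters for three cells, so the fit is exact. CARE-FAM effect = m11 − m01, with variance 2s²/n. The comparison is 74 against 74.

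By symmetry, the WEP-CARE effect becomes m11 − m10. The variance ratio is 2, so standard errors grow by √2, about 1.41. In a logistic model with family clustering the factor is only approximate. Because the three-cell fit is exact, nothing is left over to show whether additivity holds.

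**4. If the rule were meant only for families assigned an intervention**, all four cells and up to 155 TAU families would remain, and steps 2 and 3 would not apply. The article does not say this.

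**The case against.** The strongest reply has three parts.

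*The intent is clear enough.* A minimum number of sessions reads naturally as an adherence rule for families that were offered sessions, and repeating the primary analysis presupposes both levels of both factors. The article is condensed, and arm-specific criteria may stand in the full protocol or analysis plan. The authors may well have meant this. But the article gives a complete membership rule covering all families and does not limit it to the intervention arms. This is a stated rule that produces the wrong set, which is different from detail left to another document.

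*The analysis is supportive.* Only the two ITT factor contrasts are confirmatory, and they keep the TAU arm. This stands, and it limits the severity.

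*The estimates remain meaningful under the plan's independence assumption.* Under additivity, combination against WEP-CARE only estimates the same CARE-FAM effect, less precisely, and it already forms half of the ITT contrast. This also stands. What is lost is the half measured against TAU, and any means within that set of testing the assumption.

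A reader might infer more than the text supports:

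- *That power falls to about 50%.* That figure (49.2% by a normal approximation) puts 91.2% and 80% into single cells, but they are rates by CARE-FAM status, averaged over WEP-CARE. With the same effect assumed for WEP-CARE, cell rates matching those margins are 96.8% against 85.6% if risks add (power about 69%), or about 94.9% against 87.5% if log-odds add (about 36%). The answer depends on the scale, and no power is claimed for this analysis.
- *That the planned interaction test is lost.* It is a separate additional analysis, and only the primary analysis is repeated per protocol.
- *That three sessions is the wrong threshold*, because the article says of the later family sessions: "The program is concluded with about three sessions for the whole family, which are the core of the CARE-FAM intervention". Where to set the threshold is a judgement, and the earlier sessions include work with the parents, whose outcome is primary.
- *That adherence must be counted per parent.* The family is the unit of randomisation, and the article does not say that both parents must complete WEP-CARE.

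**Conclusion.** The point holds as a moderate defect confined to the supportive per-protocol analysis. The literal rule admits none of the 155 control families that follow their assignment. It leaves at most 465 families in three cells, turns each factor effect into an add-on comparison of at most 74 against 74 conspicuous parents, and roughly doubles the variance.

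The exclusion follows from the wording alone and needs no numerical assumption. The counts assume the planned cell sizes and full adherence in the active arms, so they are upper limits. The doubling further assumes equal cells and a common variance.

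It would go too far to say that the trial's conclusion is at risk, that no effect can be estimated, or that the per-protocol result could never bear on the ITT result. The confirmatory contrasts are untouched, and both effects are estimable if additivity is accepted.

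**What to change.** Replace the single membership rule with one for each randomised arm:

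- **No study intervention (TAU):** the family received neither programme within the study.
- **CARE-FAM only or WEP-CARE only:** the family met the session criterion on its assigned programme.
- **Combination:** the family met the criterion on both programmes.

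State what counts as a session for the WEP-CARE writing tasks. If the present rule was meant only for families assigned an intervention, say so in the same place.

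The cost is a few sentences. The present rule already needs session counts, and the Discussion says that sessions and writing tasks will be documented, so no new assessment of families is needed; the counts must be kept separately for each programme. Settle the wording before outcome data by arm are seen, so that membership of the set cannot be influenced by the results.

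No change is needed to the ITT analysis, the sample size or the randomisation.

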#### Sample size

Sample size calculation was carried out with the software PASS 2015, using two independent proportions and is based on the assumed increase in the proportion of non-conspicuous parent among the initially conspicuous parents according to SCID-I criteria between the patients treated with CARE-FAM and patients that did not receive CARE-FAM at18 months after randomization. Additionally, we assume the same effect size between patients with and without WEP-CARE. Furthermore, we suppose that the two interventions work independently of each other. Given a power of 80% and a type I error rate of 5% (two-sided hypothesis), 74 initially conspicuous parents per treatment combination group (296 in total) are needed to detect a difference of 11.2% (91.2% of the CARE-FAM patients and 80% of the non-CARE-FAM patients) in the proportion of non-conspicuous parents between both groups. We further assume that at the beginning of the study 30% of the parents are conspicuous. So, at the end of the study, a total of 988 parents must be available for evaluation. Additionally, we expect a dropout rate of 20% between baseline and follow up. To compensate for this, a total of 1236 parents must be recruited. This means that a total of 618 (rounded up to 620) families (310 per stratum CARE-FAM yes/no, 155 families per group of the four randomization groups: CARE-FAM only, WEP-CARE only, combination, no study intervention) has to be included in the trial.

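### LOCF is a weak sensitivity check here: every analysed parent is conspicuous at baseline, so a parent with no later SCID-I is scored a failure or left unimputed

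*Protocol article*

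**What the plan says.** In the Data analysis section, the primary mixed logistic model for the binary SCID-I diagnosis "within the ITT population of all initially conspicuous parents is performed". The ITT population is defined by available baseline documentation, so a parent who is never seen again still belongs to it. The T4 (18-month) contrasts of the two intervention factors are the only confirmatory results, and the primary analysis has its own handling of missing values. After that, in a series of sensitivity analyses, "missing values are imputed by different approaches as last observation carried forward, multiple imputation, worst- and best-case imputations".

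Table 2 schedules the SCID-I, BSI and PHQ-D at baseline and at 6, 12 and 18 months. The Sample size section assumes non-conspicuous proportions at 18 months of "91.2% of the CARE-FAM patients and 80% of the non-CARE-FAM patients", and adds that "we expect a dropout rate of 20% between baseline and follow up". It does not divide that dropout by arm or by visit. The article does not say whether a baseline SCID-I may be carried forward.

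**The concern.** LOCF is informative only if the last observed status says something about the missing one. Here the baseline status is the same for everyone analysed. For a parent lost before the 6-month visit (T2), the last SCID-I is the one that qualified the parent for the analysis. There are then two readings:

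- Baseline is carried forward. The parent is scored conspicuous at 18 months, although the plan expects at least four in five to recover. If worst case means that all missing parents are conspicuous, LOCF gives these parents the same value as that analysis.
- Baseline is not carried forward. The parents with no follow-up stay unimputed, and they are the ones for whom an ITT sensitivity analysis is most needed.

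Under the first reading the LOCF contrast moves with any difference in early dropout between the levels of a factor, even when dropout is unrelated to outcome within each level. Such a difference is possible in either direction. Families know their allocation. Controls receive nothing from the study, while treated families face six to eight sessions, 12 writing tasks, or both. At stake is how the robustness of the primary result is judged, not the primary result itself.

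**Working it through.** **Inputs from the Sample size section.** 91.2% versus 80% non-conspicuous at 18 months; 74 evaluable conspicuous parents per cell, hence 148 per factor level; 30% conspicuous at baseline; 20% dropout; two-sided 5%, 80% power.

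**The plan's own figure.** The unpooled two-proportion formula gives n = (zα + zβ)² × S ÷ 0.112² = 150.3, where zα = 1.960, zβ = 0.842 and S = 0.912×0.088 plus 0.80×0.20. That is 151 per level against 148 stated (2.0% off). Power at 148 per level is 78.7%. The recruitment chain reproduces exactly per cell: 74 ÷ 0.30 → 247, ×4 = 988; 247 ÷ 0.80 → 309, ×4 = 1236. The planning basis is therefore sound for what follows.

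**Parents per level before dropout.** 148 ÷ 0.80 = 185.

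**LOCF proportion.** Let p be the true 18-month proportion non-conspicuous, d the dropout, e the share of dropouts with no post-baseline SCID-I, and h the remission rate at the last visit of later dropouts relative to the 18-month rate. With baseline carried forward and dropout unrelated to outcome:

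P(non-conspicuous) = p(1 − d) + d(1 − e)·p·h

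The split of d by level, and e and h, are assumptions. With h = 1:

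| Dropout, CARE-FAM yes / no | Share before T2 | LOCF proportions | Difference (true 11.2) | Difference if no true effect (80% both) |
|---|---|---|---|---|
| 20% / 20% | all | 73.0% / 64.0% | 9.0 | 0.0 |
| 20% / 20% | half | 82.1% / 72.0% | 10.1 | 0.0 |
| 25% / 15% | all | 68.4% / 68.0% | 0.4 | −8.0 |
| 25% / 15% | half | 79.8% / 74.0% | 5.8 | −4.0 |
| 15% / 25% | all | 77.5% / 60.0% | 17.5 | +8.0 |
| any of these | none | 91.2% / 80.0% | 11.2 | 0.0 |

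Example: 0.912×0.75 = 0.684 and 0.80×0.85 = 0.680.

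**Rejection rates**, from a simple two-proportion test at 185 per level that ignores family clustering:

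- Equal 20% early loss: power about 46%; rejection under no true effect stays at 5%.
- 25% / 15% early loss with no true effect: 0.60 versus 0.68. The standard error under the null is √[2×0.64×0.36 ÷ 185] = 0.0499. Under the alternative it is √[V ÷ 185] = 0.0497, where V = 0.60×0.40 plus 0.68×0.32. Rejection is Φ[z] with z = [0.08 − 1.96×0.0499] ÷ 0.0497, or about 36%, plus a negligible upper tail.

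**Gap that cancels the planned effect.** Solving 0.912×[0.80 − x] = 0.80×[0.80 + x] gives x = 0.112×0.80 ÷ 1.712 = 0.052. That is early losses of 25.2% versus 14.8%, a gap of 10.5 points.

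**If later dropouts carry less remission (h = 0.7).** With no loss before T2, equal 20% dropout gives 10.5 points, and 25% / 15% gives 8.0 points (−2.4 if there is no true effect). So the absence of distortion for later losses depends on h = 1.

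**The case against.** The strongest case on the other side has four parts.

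- **Only losses before T2 are forced to failure.** A reader might infer that LOCF scores all dropouts as failures, or that it measures dropout rather than robustness. The documents do not support this. The SCID-I is repeated at 6 and 12 months, so later dropouts may carry a recovered status. About 80% of outcomes are expected to be observed, and equal dropout attenuates the effect without raising type I error. This objection stands.
- **The confirmatory conclusion is not at risk.** LOCF is one of four supplementary approaches, and missing counts are reported by treatment group, so unequal dropout would be visible beside it. This also stands.
- **The 25% / 15% split is an assumption close to the break-even point.** It is also hard to reach in a factorial design, because half of the non-CARE-FAM level receives WEP-CARE. If all three therapy cells lost 25%, the control cell would have to lose only 5% for that level to average 15%. The payment for completing follow-up and the full baseline diagnostics apply to all groups. This is why the size is given as a range.
- **Carry-forward rules, the definition of worst case and any intermediate analysis may be in the analysis plan.** A reader might infer that nothing is planned between multiple imputation and the extremes. The article's list can be read as examples, so that is not claimed here.

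The method itself remains open to criticism. LOCF is a stated choice, and neither reading of it serves parents with no follow-up well.

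**Conclusion.** The point holds in a limited form. Because the analysed parents are uniformly conspicuous at baseline, LOCF imputes failure for those with no post-baseline SCID-I, or leaves them unimputed, and so adds little as a robustness check.

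If baseline is carried forward, the apparent CARE-FAM effect under LOCF ranges from 0.4 to 17.5 points around the planned 11.2 in the scenarios shown. It is 9.0 points under equal early loss. It is undistorted if all loss comes after T2 and later dropouts carry the 18-month remission rate. These figures rest on an assumed split of the 20% dropout by level and visit, on dropout unrelated to outcome within level, and on an unclustered two-proportion calculation. The same reasoning applies to the WEP-CARE factor, for which the plan assumes the same effect size.

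The primary test is unaffected. This is a cheap improvement of low severity.

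**What to change.** Replace LOCF in the list of sensitivity analyses with delta-adjusted multiple imputation. Impute the 18-month SCID-I status under missing at random, by arm, using the 6- and 12-month SCID-I, BSI, PHQ-D and baseline data. Then lower the odds of recovery in missing parents stepwise over a prespecified delta range, varied by arm, until the conclusion changes (the tipping point). Keep the worst- and best-case imputations as outer bounds.

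The cost is a change of wording, some programming and the need to fix a delta range in advance. No new data are required: multiple imputation is already planned, and these instruments are scheduled at every visit.
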